### **8.10 Trial restrictions**

The trial restrictions in terms of interactions with other therapies are described in section 8.8.

### **8.11 Assessment of compliance with treatment**

Compliance with study medication will be assessed at the 1, 2, 3 and 4 week titration assessments and the 6 and 12 month assessments. Outwith pandemics, participants will be asked to return empty drug bottles. Compliance will be calculated by pill counting. During pandemics this will not be possible. Instead, participants will be asked to return any unused study medication to their local pharmacy and ask them to safely dispose of the medication. In these circumstances, no pill count will be possible. Participants will also be asked to estimate their compliance at each visit.

### **8.12 Name and description of each Non-Investigational Medicinal Product (NIMP)**

There are no NIMPs within this trial. During follow-up, participants should continue to take any existing medication, and any new medication prescribed for them (8.10) but these are not supplied to the participant within this protocol.

## 9 PHARMACOVIGILANCE

### 9.1 Definitions

| Term                                                         | Definition                                                                                                                                                                                                                                                                                                                                                                                                                                                                                                                                                                                                                                                                                                                                                                                                                                                             |
|--------------------------------------------------------------|------------------------------------------------------------------------------------------------------------------------------------------------------------------------------------------------------------------------------------------------------------------------------------------------------------------------------------------------------------------------------------------------------------------------------------------------------------------------------------------------------------------------------------------------------------------------------------------------------------------------------------------------------------------------------------------------------------------------------------------------------------------------------------------------------------------------------------------------------------------------|
| Adverse Event (AE)                                    | Any untoward medical occurrence in a participant to whom a medicinal product has been administered, including occurrences which are not necessarily caused by or related to that product.                                                                                                                                                                                                                                                                                                                                                                                                                                                                                                                                                                                                                                                                              |
| Adverse Reaction (AR)                                 | An untoward and unintended response in a participant to an investigational medicinal product which is related to any dose administered to that participant. The phrase "response to an investigational medicinal product" means that a causal relationship between a trial medication and an AE is at least a reasonable possibility, i.e. the relationship cannot be ruled out. All cases judged by either the reporting medically qualified professional or the Sponsor as having a reasonable suspected causal relationship to the trial medication qualify as adverse reactions. It is important to note that this is entirely separate to the known side effects listed in the SmPC. It is specifically a temporal relationship between taking the drug, the half-life, and the time of the event or any valid alternative etiology that would explain the event. |
| Serious Adverse Event (SAE)                           | A serious adverse event is any untoward medical occurrence that: 
 
• results in death
 
• is life-threatening
 
• requires inpatient hospitalisation or prolongation of existing hospitalisation
 
• results in persistent or significant disability/incapacity
 
• consists of a congenital anomaly or birth defect
 
 Other 'important medical events' may also be considered serious if they jeopardise the participant or require an intervention to prevent one of the above consequences.
NOTE: The term "life-threatening" in the definition of "serious" refers to an event in which the participant was at risk of death at the time of the event; it does not refer to an event which hypothetically might have caused death if it were more severe.                             |
| Serious Adverse Reaction (SAR)                        | An adverse event that is both serious and, in the opinion of the reporting Investigator, believed with reasonable probability to be due to one of the trial treatments, based on the information provided.                                                                                                                                                                                                                                                                                                                                                                                                                                                                                                                                                                                                                                                             |
| Suspected Unexpected Serious Adverse Reaction (SUSAR) | A serious adverse reaction, the nature and severity of which is not consistent with the information about the medicinal product in question set out in the reference safety information: 
 
• in the case of a product with a marketing authorisation, this could be in the summary of product characteristics (SmPC) for that product, so long as it is being used within its licence. If it is being used off label an assessment of the SmPCs suitability will need to be undertaken.
 
• in the case of any other investigational medicinal product, in the investigator's brochure (IB) relating to the trial in question
 
                                                                                                                                                                                   |

NB: to avoid confusion or misunderstanding of the difference between the terms "serious" and "severe", the following note of clarification is provided: "Severe" is often used to describe intensity of a specific event, which may be of relatively minor medical significance. "Seriousness" is the regulatory definition supplied above.

The severity of SAEs will be assessed using the following definitions;

- **Mild:** an event that is easily tolerated by the trial participant, causing minimal discomfort and not interfering with everyday activities.
- **Moderate:** an event that is sufficiently discomforting to interfere with normal everyday activities.
- **Severe:** an event that prevents normal everyday activities.

## 9.2 Operational definitions for (S)AEs

In this trial:

- SAEs will be recorded from the time a participant consents to join the study until the end of the weaning period after the 12 month follow-up (see notes in section 8.7.2). Participants who withdraw from taking the study drug during the 12 month follow-up period will have SAEs recorded from the time the participant consents to join the study until 28 days after ceasing study medication. Participants who never start taking the study drug will have SAEs recorded for 28 days from the time they consent to join the study. All adverse reactions will be recorded for the same period of time described above.
- Hospitalisations for treatment planned prior to randomisation and hospitalisation for elective treatment of a pre-existing condition will **not** be considered or recorded or reported as an SAE. Complications occurring during such hospitalisation will also not be considered, recorded or reported as an SAE – unless there is a possibility that the complication arose because of the study medication (i.e. a possible adverse reaction).
- Exacerbations of COPD or hospital admissions as a consequence of exacerbations of COPD will **not** be considered as AEs or SAEs because they are primary and secondary outcomes for the trial. These will be recorded as part of the trial outcomes, but will not be considered or recorded or reported as AEs or SAEs. Confirmed cases of pneumonia should be captured as SAEs.

All other SAEs (including SARs) should be reported to the trial office.

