| Health care utilisation                                                      | ✓           |        |         |         |         | ✓                         | ✓                          |                          |                             |
| Patient Compliance                                                           |             | ✓      | ✓       | ✓       | ✓       | ✓                         | ✓                          |                          |                             |
| Telephone call to confirm cessation of study drug                            |             |        |         |         |         |                           |                            |                          | ✓                           |

- \* If remote assessment being conducted self reported height and weight will be recorded.
- \*\* If remote assessment being conducted these will be measured using a supplied digital sphygmomanometer.
- + During the COVID-19 pandemic, lung function (an aerosol generating procedure) will not be assessed.

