### **8.7.2 Dose reduction at end of follow-up**

Following completion of the 12 month dosing period participants will be weaned off study drug over the following weeks (3-2-1 tablet(s) od) in order to avoid possible rebound myocardial ischemia. A similar regime will be recommended for participants who wish to discontinue medication during the study.

| Maintenance dosage: | At final visit | Subsequent week |       |      |
|---------------------|----------------|-----------------|-------|------|
|                     |                | 1               | 2     | 3    |
| 1 tab               | Stop           |                 |       |      |
| 2 tab               | 1 tab          | stop            |       |      |
| 3 tab               | 2 tab          | 1 tab           | stop  |      |
| 4 tab               | 3 tab          | 2 tab           | 1 tab | stop |

Successful weaning will be confirmed by the research nurse by telephone one week after anticipated cessation of treatment. Successful weaning is defined as reduction of dose as described above prior to stopping. Any adverse effects experienced during weaning will be documented within the CRF.

Figure 3: Schematic representation of dose titration

[figure not shown]

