### 9.6.1 Contraceptive requirements and pregnancy testing

Women who are eligible to take part in the trial and are of child bearing potential (i.e. are not post-menopausal (defined as 12 months with no menses without an alternative medical cause) or permanently sterilised) will be advised to use two forms of highly effective birth control (i.e. results in a less than 1% per year failure rate) and continue use until at least 28 days after last dose of trial medication. Acceptable forms of contraception include:-

- Established use of oral, transdermal, injected or implanted hormonal methods of contraception.
- Placement of an intrauterine device (IUD) or intrauterine system (IUS).
- Barrier methods of contraception: Condom or Occlusive cap (diaphragm or cervical/vault caps) plus a spermicidal foam/gel/film/cream/suppository.
- Male partner is sterile (with the appropriate post-vasectomy documentation of the absence of sperm in the ejaculate) prior to female entry onto the trial and is the sole partner of the female participant.
- True abstinence: When this is in line with the preferred and usual lifestyle of the subject. [Periodic abstinence (e.g., calendar, ovulation, symptothermal, post-ovulation methods) and withdrawal are not acceptable methods of contraception for trial purposes].

Women who are of child bearing potential should have a pregnancy test seven days or fewer before the first dose of study medication. For women who attend a face-to-face recruitment visit, the pregnancy test can be conducted then. For women recruited without a face-to-face recruitment visit, a pregnancy test can be sent at the same time as the sphygmomanometer and women will be asked to report the results of the pregnancy test during the recruitment assessment. Women of child bearing potential should also have a pregnancy test at the end of titration and at the 6 and 12 month assessments. Women will be sent the pregnancy test around the time of the visit and be asked to report the results of the pregnancy test to the research nurse.

The SmPC for bisoprolol does not warn against the use of bisoprolol in men because of teratogenic effects [35]. No contraception measures are needed for male subjects with pregnant or non-pregnant partner.

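### For participants who complete treatment, SAE and adverse-reaction recording closes at the last tablet, while early stoppers are recorded for 28 days, so non-fatal events after the final stop are missed for most of the trial

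*Protocol*

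**What the plan says.** Section 9.2 sets two recording windows in one bullet. SAEs in participants who complete treatment are recorded "until the end of the weaning period after the 12 month follow-up", with a pointer to section 8.7.2. Those who come off study drug early are recorded "until 28 days after ceasing study medication". Adverse reactions follow the same windows: "All adverse reactions will be recorded for the same period of time described above".

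Section 8.7.2 steps the dose down after the 12-month visit "in order to avoid possible rebound myocardial ischemia". Its table takes participants on 4, 3 and 2 tablets to zero over three, two and one weeks. Those on 1 tablet stop at the final visit. Adverse effects during weaning are to be documented in the CRF. The section then provides a contact: "Successful weaning will be confirmed by the research nurse by telephone one week after anticipated cessation of treatment". It also defines the term: "Successful weaning is defined as reduction of dose as described above prior to stopping".

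Section 7.8 times the call by dose and describes it only as confirming that weaning succeeded. In Table 2 (section 7.6), the column for the period after weaning has one tick, on the row "Telephone call to confirm cessation of study drug". The adverse-event and MACE rows are blank there. The text of 7.6 ascertains reactions and SAEs while participants are on study medication, and MACE at 6 and 12 months. Section 9.5 requires every death to be reported and gives no end date.

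**The concern.** The protocol names a risk that can arise on stopping treatment, and every participant who completes treatment stops. Part of that risk lies after the last dose. For completers, 9.2 closes the window at that moment. A participant admitted with a non-fatal myocardial infarction four days after the last tablet falls outside the SAE window, and no scheduled MACE assessment follows.

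The two windows in 9.2 also differ without a stated reason, and the shorter one applies to the larger group. At stake is how completely the trial describes safety around discontinuation. Efficacy is not affected.

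**Working it through.** There is no power or sample-size figure to test here. The check is a timeline and a head count.

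**Timeline.** Inputs: stop week from the 8.7.2 table, call week from 7.8, both counted from the 12-month visit. Gap = 7 × (call week − stop week).

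| Final dose | Last step (8.7.2) | Call (7.8) | Stop to call | 28 days after stop |
|---|---|---|---|---|
| 1 tablet | week 0 | week 1 | 7 days | week 4 |
| 2 tablets | week 1 | week 2 | 7 days | week 5 |
| 3 tablets | week 2 | week 3 | 7 days | week 6 |
| 4 tablets | week 3 | week 4 | 7 days | week 7 |

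The 7-day gap at every dose reproduces the one week stated in 8.7.2, so the call schedule is internally consistent.

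**Recording after the last dose.**
- Completers, as written: window end − last dose = 0 days. On 1 tablet there is no step-down, so recording ends at the 12-month visit.
- Early stoppers, as written: 28 days.
- Completers, if the window ran to the existing call: 7 days.
- Completers, if aligned with early stoppers: 28 days, which is 28 − 7 = 21 days beyond the existing call.

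**How many participants.** Inputs: target of 1,574 and 15% stopping study drug (10.1); about 6% deaths and about 15% lost to follow-up within 12 months (10.3). The protocol does not say how these three groups overlap.
- Deaths and losses all fall among those who stop treatment: 1,574 × (1 − 0.15) = 1,338, or 669 per arm.
- No overlap: 1,574 × (1 − 0.15 − 0.06 − 0.15) = 1,574 × 0.64 = 1,007, or about 504 per arm.
- Early stoppers with the 28-day window: 1,574 × 0.15 = 236.

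These are counts of people whose window closes at the last dose, not of missed events. The protocol gives no event rate after cessation, so the number of missed events cannot be estimated from it.

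**The case against.** A reader might infer that the trial will be unable to say anything about the safety of stopping bisoprolol, or that any excess on withdrawal would be invisible to the data monitoring committee. The documents do not support that. On 2 to 4 tablets the step-down of one to three weeks is inside the window, and 8.7.2 asks for adverse effects during weaning to be documented. Fatal events are reportable under 9.5 whenever they occur. Early stoppers contribute 28 days in both arms, and under 7.10 some of them stop without weaning. What is lost is non-fatal events after the final stop in completers.

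The end of the window can also be read more generously. Section 9.2 refers to the notes in 8.7.2, and those include the confirmation call, so a site might keep recording until then. The definition of successful weaning in 8.7.2 and the heading of the Table 2 column point the other way. Even on the generous reading, completers have 7 days against 28. Similarly, the blank cells in Table 2 may be an omission: the call is the only scheduled contact after month 12, so adverse effects during weaning would probably be collected there. That would be a reason to complete the table.

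The protocol also plays the risk down. Section 8.7.2 calls rebound only possible. Section 7.10 says weaning is advised for cardiovascular indications, which do not apply here, and Appendix 1 accepts immediate stopping on similar grounds. Heart failure, and infarction or acute coronary syndrome within the past year, are exclusions. Safety of withdrawal is not a stated objective. These points lower the likely yield, and any claim that the reported safety profile would be too favourable is conjecture. They do not explain why completers get a shorter window than early stoppers.

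Finally, the 28-day contraception rule in 9.6.1 serves another purpose and lends no support to an SAE window. The only relevant comparator is the early-stopper rule in 9.2.

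**Conclusion.** The point holds in limited form. As written, 9.2 gives completers 0 days of SAE and adverse-reaction recording after the last dose, against 28 days for early stoppers, and the existing call falls 7 days outside the completers' window. This affects roughly 1,000 to 1,340 of 1,574 participants, assuming the recruitment target is met and the protocol's own rates of stopping, death and loss apply.

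The loss is confined to non-fatal events after the final stop. The 12-month safety comparison, the primary outcome and the sample size are untouched. This is a worthwhile, low-cost improvement to safety ascertainment. It does not threaten the trial's main result.

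**What to change.** In 9.2, extend completers' recording of SAEs and adverse reactions at least to the telephone call one week after cessation, or align it with the 28 days already used for early stoppers. State the end point as a number of days after the last dose, so that it no longer depends on how the weaning period is read. Tick adverse events/reactions and MACE in the post-weaning column of Table 2, and ask about both at that contact. Report events after the last dose by arm as a separate period, leaving the 12-month comparison as planned.

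The shorter option needs no new contact, only added questions and a few more SAE reports, each with record review, causality assessment and 24-hour reporting under 9.3. The 28-day option also needs a contact about 21 days later than the present call, with matching edits to 7.6, 7.8 and 8.7.2. If the existing call were moved rather than supplemented, confirmation of cessation would be delayed by the same three weeks.

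Separately, 7.10, 8.7.2 and Appendix 1 describe the withdrawal risk and the handling of stopping differently, and should be reconciled by those responsible for clinical management. The recording change alters neither dosing nor weaning.

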### **3.2 Secondary objectives**

The secondary objectives are to compare the following outcomes between participants treated with bisoprolol, and those treated with placebo:

- Hospital admissions with a primary diagnosis of COPD exacerbation.
- Total number of emergency hospital admissions.
- Total number of major adverse cardiovascular events (MACE).
- Lung function (during the COVID-19 pandemic, lung function cannot be assessed in participants).
- Changes in breathlessness during treatment.
- All-cause, respiratory and cardiac mortality.
- Drug reactions and serious adverse events.
- Health related quality of life.
- Disease specific health status.
- Health care utilisation.
- Incremental cost-per-exacerbation avoided.
- Costs to the NHS and patients and lifetime cost-effectiveness based on extrapolation modelling.
- Modelled lifetime incremental cost per Quality Adjusted Life Year.
- Treatment effects in participants with and without clinically diagnosed heart disease.

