#### *Adverse reactions and serious adverse events*

Adverse reactions and serious adverse events whilst on study medication will be ascertained at the 1, 2, 3 and 4 week titration assessments and the 6 and 12 month assessments. Serious adverse events/drug reactions will be subject to the serious adverse events reporting protocol (see section 9 for further details).

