#### *Mortality*

Deaths during the follow-up period will be reported as a SAE.

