### 10.3 Statistical analysis plan

Statistical analyses will be according to the intention to treat principle with a per protocol analysis performed as a sensitivity. The per protocol analysis will exclude participants who were not compliant (at less than 70%) with their study medication. All analyses will be governed by this comprehensive SAP which will be agreed by the Trial Steering Committee (TSC) and approved by the independent Data Monitoring Committee (DMC) prior to any analyses being undertaken. Unless pre-specified, a 5% two-sided significance level will be used to denote statistical significance throughout. There will be no interim analyses undertaken. In line with other recent COPD trials it is not envisaged that the DMC will be monitoring the study in order to terminate it prematurely on finding evidence of overwhelming benefit – nor will they terminate it for futility.

The primary outcome - number of COPD exacerbations requiring antibiotics and/or oral corticosteroids in the 12 months after randomisation - will be compared between randomised groups using negative binomial regression with length of time in the study as an offset. Estimates will then be adjusted for centre and other baseline covariates that are known to be strongly related to outcome (e.g. age, smoking, COPD hospitalisations in year prior to study – these will be pre-specified in the SAP). Despite the patients being followed-up for a single year, some will withdraw early and, given their chronic illness, some will inevitably die. Use of an overdispersion parameter should improve the model estimates as it takes between patient variability in exacerbation rate into account. The negative binomial model assumes that each patient has their own underlying exacerbation rate which follows a Poisson distribution, but the expected rate is allowed to vary across patients according to a gamma distribution. The shape parameter from the gamma distribution explicitly represents the variability between patients. The negative binomial model coincides with the Poisson model when this dispersion parameter is zero. Assumptions of this model are that exacerbation counts are assumed to vary about means that differ for each patient, with means varying across the population. Hence, the negative binomial model more effectively accounts for increased exacerbation events amongst patients withdrawing early.

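### Section 9.2 ends SAE and adverse-reaction recording 28 days after study drug stops, so the planned randomised SAE comparison rests on windows that depend on tolerance

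*Protocol*

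**What the plan says.** Protocol section 9.2 sets three recording windows.

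- Completers: "SAEs will be recorded from the time a participant consents to join the study until the end of the weaning period after the 12 month" assessment.
- Those who stop drug during the year: from consent "until 28 days after ceasing study medication".
- Those who never start: "Participants who never start taking the study drug will have SAEs recorded for 28 days from the time they consent to join the study".

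Adverse reactions follow suit: "All adverse reactions will be recorded for the same period of time described above". The assessment text in section 7.6 is narrower still: "Adverse reactions and serious adverse events whilst on study medication will be ascertained at the 1, 2, 3 and 4 week titration assessments", and again at 6 and 12 months.

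Section 3.2 lists "Drug reactions and serious adverse events" among the outcomes to be compared between bisoprolol and placebo, and section 3.4 lists SAEs and adverse reactions as a secondary outcome. Section 10.3 opens with "Statistical analyses will be according to the intention to treat principle". For adverse events it plans descriptive statistics and, where judged suitable, a chi-squared test, t-test or similar. Poisson regression is optional for repeated events, and no time offset is stated for it. The primary-outcome model does have one.

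Section 7.10 asks participants withdrawn from treatment to stay on the full follow-up schedule or, failing that, to allow use of their routine records. On deaths, section 7.6 says: "Deaths during the follow-up period will be reported as a SAE". Section 9.5 requires every death to be reported on the SAE form, whatever its cause.

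**The concern.** A treatment-plus-28-days window is a normal rule for safety reporting. Here the same rule also defines the data for a randomised secondary outcome. Under intention to treat, a participant who stops at week 4 stays in the denominator for the year but can contribute SAEs for only 8 weeks.

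Stopping is not a neutral event. Section 7.10 lists unacceptable adverse effects, intercurrent illness and serious disease among the reasons for withdrawal. In section 8.7.1, low heart rate or low blood pressure with symptoms can take the dose down to zero. Recording therefore ends early in people selected for intolerance or illness.

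What is at stake is the completeness and comparability of the remaining safety data on an off-label beta-blocker in COPD. The SAP, which is not shown, could add a person-time offset. It could not recover events that were never recorded, nor correct for stoppers having a different later risk.

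**Working it through.** **Inputs from the protocol**
- Windows: section 9.2. Weaning adds 0 to 3 weeks after week 52, depending on final dose (section 8.7.2).
- Stopping: about 15%, not split by arm (section 10.1).
- Arm size: 787 (section 10.1).

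The arm size is used only for scale. With a difference of 0.33 and an SD of 1.86, n = 2 × (1.960 + 1.282)² × 1.86² / 0.33² = 668 per arm, against 669 stated; 669 / 0.85 = 787. The protocol states no power for SAEs.

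**Step 1: length of the window.** Stopping at week s gives s + 4 weeks. Time between consent and first dose is ignored.

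| Participant | Weeks recorded | Share of 55 |
|---|---|---|
| Completer | 52 to 55 | up to 100% |
| Stops week 26 | 30 | 55% |
| Stops week 13 | 17 | 31% |
| Stops week 4 | 8 | 15% |
| Never starts | 4 | 7% |

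For a non-starter the clock runs from consent, which precedes randomisation, so part of the 4 weeks may fall before randomisation.

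**Step 2: time unrecorded with equal stopping.** Fraction lost = d × [55 − (s + 4)] / 55, with d = 0.15.
- s = 4: 0.15 × 47/55 = 12.8%
- s = 13: 0.15 × 38/55 = 10.4%
- s = 26: 0.15 × 25/55 = 6.8%

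Planned time is 787 × 55/52 = 832 person-years per arm, so about 57 to 107 are lost. Against 52 weeks instead of 55, the range is 0.15 × 22/52 = 6.3% to 0.15 × 44/52 = 12.7%.

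**Step 3: ratio of observation time, bisoprolol to placebo.** R = [(1 − dB) × 55 + dB × (s + 4)] / [(1 − dP) × 55 + dP × (s + 4)]. The arm-specific rates are assumed.

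| Stopping, bisoprolol v placebo | s = 4 | s = 13 | s = 26 |
|---|---|---|---|
| 15% v 15% | 1.00 | 1.00 | 1.00 |
| 18% v 12% | 0.943 | 0.955 | 0.971 |
| 20% v 10% | 45.6/50.3 = 0.907 | 47.4/51.2 = 0.926 | 50.0/52.5 = 0.952 |

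If placebo participants stopped more often, the ratios would invert and the distortion would run the other way.

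**Step 4: what that could do to a test of proportions.** Further assumptions: a constant SAE rate r of 0.2 to 0.4 per person-year, the same in stoppers and non-stoppers. The expected proportion with an SAE is (1 − d)(1 − exp(−r × 55/52)) + d(1 − exp(−r(s + 4)/52)).
- No true difference, 20% v 10%: for r = 0.2 and s = 4, 0.1586 against 0.1746, a risk ratio of 0.91. For r = 0.4 and s = 26, 0.3172 against 0.3311, a ratio of 0.96. A nominal 5% test rejects 7% to 23% of the time across these cases.
- Assumed true rate ratio 1.3 with r = 0.2, 20% v 10%: a risk ratio of 1.26 appears as 1.15 to 1.21, and power falls from 67% to between 25% and 46%.
- The same true effect with 15% v 15%: the risk ratio stays at 1.26, but power falls from 67% to between 60% and 64%, because events are lost.

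**The case against.** The strongest reply has four parts.

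1. **The most serious events are collected by other routes.** MACE is ascertained at 6 and 12 months, with attempted record checks for non-attenders and no 28-day limit (section 7.6). All deaths are reported (sections 7.6 and 9.5), and mortality has its own log-rank analysis. COPD exacerbations and the admissions that they cause are excluded from SAEs and analysed with a time offset. This stands and narrows the point. All-cause emergency admissions cover part of what is left, but section 7.6 words their collection as on study medication, so they do not clearly close the gap.
2. **The documents do not show bias.** Section 8.7.1 expects similar intolerance in both arms, citing heart failure trials, and section 10.1 gives one stopping rate for both. This also stands. A reader might infer that the rule makes bisoprolol look safer; the protocol does not support that as a statement of fact.
3. **The analysis is not fixed.** The comparison is conditional, Poisson regression is allowed, and an offset is properly a matter for the SAP. That is correct for the analysis, but the collection window is fixed in the protocol.
4. **A longer window can dilute a drug effect with off-drug time.** True, and a reason to report both analyses rather than replace one with the other.

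The discrepancy on deaths is small. Reading 7.6 and 9.5 as specific rules that override 9.2 loses no death, but 9.2 does not say so.

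**Conclusion.** The point holds in a limited form. It is certain from the text that recording windows differ between participants according to treatment tolerance. If the expected 15% stop between weeks 4 and 26, roughly 7% to 13% of person-time is unrecorded for this outcome. The affected events are non-fatal, non-MACE, non-COPD SAEs, including confirmed pneumonia, and adverse reactions.

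Bias between arms is conditional. It requires stopping to differ in number, timing or type of participant. The 0.91 to 0.95 ratio rests on an assumed 20% v 10% split, and the test results on assumed SAE rates; equal number and timing give a ratio of 1.00. It would go too far to say that the main safety comparison is biased, or that later deaths and major cardiac events are missed. This is an inexpensive improvement to data collection, not a defect that undermines the trial.

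**What to change.** Amend section 9.2, and the matching text in 7.6, as follows.

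- For the randomised comparison, record SAEs to a common 12 months from randomisation in every participant who has not withdrawn from follow-up, on drug or not. Use the 6- and 12-month contacts and the record access already planned.
- Report an on-treatment-plus-28-days analysis alongside, with person-time denominators, and label each analysis for what it estimates.
- Keep the 28-day rule for safety reporting.
- Reconcile 9.2 with the text on deaths in 7.6 and 9.5, for example by stating that deaths are reported throughout follow-up whatever the treatment status.

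The cost is one protocol amendment and extra SAE forms arising from roughly 15% of participants (0.15 × 1,574, about 236 people, of whom only those with late events need a form). The 12-month analysis will include off-drug time that can dilute a drug effect, which is why both analyses are reported.
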